### Immuno-monitoring

It is known that the immune system can protect against the development of cancer. This follows the normal immune response involving uptake of tumor antigens by dendritic cells (DC), presentation of these antigens in TDLN to naive CD4+ and CD8+ T cells, which will subsequently result in T cell priming, skewing and activation, expansion of CD8+ cytotoxic T cells and CD4+ T helper (Th) cells and the induction of a tumor specific response. Unfortunately the immune system is not always capable of killing all the tumor cells, or the tumor cells have successfully adapted such that the immune system does not recognize them anymore, leading to tumor escape, outgrowth and metastases.

Multiple mechanisms can be involved in this immune escape and several of these have been described to occur in HNSCC development, such as downregulation of HLA molecules preventing T cell recognition, secretion of tumor-derived immune suppressive factors (cytokines like TGF-beta or IL-10), inability of T-cells to infiltrate the tumor, attraction of immature, suppressive myeloid cells from the bone-marrow, loss of expression of co-stimulatory molecules and increased expression of inhibitory receptors and ligands or suppression of immune response by promoting the development and expansion of Tregs [42-44].

The composition of the tumor immune infiltrate can affect and may predict response to therapy, both to conventional therapies like chemoradiation and to immunotherapy with checkpoint inhibitors. It can also provide leads as to why certain patients do and others do not respond to agents targeting the PD-1/PD-L1 pathway [45]. What type of immune infiltrate is present in HNSCC can also be determined by the site of the tumor (oral cavity, oropharynx, larynx) and has not been studied in great detail yet. Similarly to other tumor types, enhanced CD8+ T cell infiltration in the tumor is associated with a better prognosis in HNSCC [46]. Interestingly, unlike in most other cancer types, there have been reports that increased Treg frequencies correlate with a good prognosis in HNSCC (reviewed in Fridman et al 2012 [47]). This could reflect a general high immune infiltration, including CD8 T cells, suggestive of an active anti-tumor immune reaction at play with collateral Treg infiltration. Tsujikawa et al. recently published an IHC-based study in a small group of 38 HNSCC patients, showing that a T cell inflamed immune signature, as well as a hypo-inflamed immune signature (little to no T cell or myeloid cell activation) were associated with good prognoses, while tumors with a myeloid inflamed profile displayed poor survival (independent of HPV status) [48]. In addition, there are several indications that head and neck cancers impact the general immune system. For example the absence of specific immune cell subsets is associated with clinical outcome [49]. In addition, the white blood cells in head and neck cancer patients have undergone markedly molecular changes [50].

We will perform extensive immune monitoring to assess baseline immune status as well as changes in immune cell infiltrate in tumor specimen prior to and after neo-adjuvant nivolumab using flow cytometry on single cell suspensions as well as six-parameter IHC staining on FFPE material. Similar analyses will be performed on surgically removed lymph nodes, as well as additionally obtained biopsies in case of heterogeneous result on baseline PET imaging). Additionally we will monitor changes in systemic immune responses by profiling peripheral blood at several time points during the treatment (as indicated), analysing frequencies and activation status of T cell subsets, peripheral blood dendritic cells and myeloid derived suppressor cells. We anticipate that we will find either pre-treatment immune traits or alterations in immune activation and immune infiltrate composition upon neoadjuvant nivolumab therapy.

### Genomic profiling

HNSCC is caused by smoking and excessive alcohol consumption. However, last decade it has been shown that also HPV infections cause HNSCC, particularly in the oropharynx. HPV-positive and HPV-negative tumors develop at the molecular level and are considered distinguished disease entities. In the oral cavity tumors are generally HPV-negative, and we recently showed that the HPV attributable fraction is below 3%. In fact it can be neglected in the current study, but will be determined during sequence analysis just in case.

HPV-negative HNSCC are characterized by many genetic changes including copy number alterations and mutations [28, 51, 52]. Also splice variants do occur and expression of embryonic genes that might all function as neoantigens. Standard approach at present is whole exome sequencing combined with RNAseq to identify potential neoantigens [53].

The sequencing data can also be used to determine the copy number profiles and HPV status using the off-target reads, but it is safer to perform parallel low coverage whole genome run as this is a cheap, more reliable and well validated analysis method. This is of relevance as there is a subgroup of particularly oral cancers that is characterized by few genetic changes also indicated as ‘copy-number-silent’. How this molecular subgroup relates to immune status and response to anti-checkpoint therapy, remains a major question.

Mutations and RNAseq data will be mined for neoantigens, the copy number profiles, and the data associated with immuneprofiles in the tumor, the peripheral blood and response in the tumor when occurring. With the planned number of patients, strong associations cannot be identified but the added value of these approaches in a larger RCT can be studied.

### Plasma vesicle microRNAs

Most, if not all, tumors shed nucleic acids into the circulation, including fragments of DNA and miRNAs from living and dying cells. Apart from the mutational landscape, disease specific dysregulation of miRNA expression is one of the hallmarks of HNSCC [28, 54, 55]. Due to the abundance of RNA species from numerous sources in the circulation, tumor derived RNA species are difficult to detect and monitor in whole blood samples. Plasma vesicle miRNAs have been shown suitable for disease monitoring in cancer patients [56]. HNSCC-specific plasma vesicle miRNA profiles are hypothesized to be useful for therapy response monitoring and potentially for treatment outcome prediction in patients with HNSCC. Possible associations between miRNA findings and immune parameters and changes therein will also be investigated in an integrated analysis.

### Rationale for dose selection

Patients will be treated with a single flat dose of 480mg nivolumab IV which has been recently approved as a 4-weekly dose [57]. This single dose allows for maximal treatment before surgery, as the timelines from diagnosis to surgery are strictly defined in the current guidelines.

### Rationale for endpoints

This is a feasibility study of neoadjuvant nivolumab in locally advanced oral cancer combined with [^18^F]BMS-986192 and [^18^F]-FDG PET as well as immuno-monitoring and DNA profiling on tissue and blood in order to identify biomarkers for response and investigate safety.

The primary endpoint of this study is [^18^F]BMS-986192 uptake in tumor lesions and safety and tolerability of neoadjuvant nivolumab. [^18^F]BMS-986192 tumor uptake will be quantified, tumor uptake heterogeneity between patients and within and between tumor lesions of the same patient will be assessed. These results will be correlated with [^18^F]-FDG uptake, as effective treatment with immune therapy may lead to increase in early [^18^F]-FDG uptake, as well as to (pathological) response.

The secondary endpoints include the correlation of the imaging and response data to measured blood and tissue parameters. The immune status will be assessed in the tumor by multiplex immunostaining (see section 3.10.1) and in peripheral blood and TDLN by flowcytometry for the frequency and activation status of immune subsets (see section 3.8). Cytokine profiling may be performed in plasma or from TDLN in ex vivo O/N cultures.

In addition, the presence of neoantigens and the molecular background of the tumor as copy-number-high or copy-number-silent will be determined. Neoantigen analysis will be performed by DNA sequencing using a combined approach of low coverage whole genome sequencing for copy numbers, and exome enrichment sequencing for mutations. Normal DNA from blood will be analyzed in parallel to filter SNPs. In addition RNA sequencing will be performed and the data mined as previously described [53].

# OBJECTIVES AND HYPOTHESES

## Primary objectives & hypotheses

1. To investigate heterogeneity in tumor uptake of [^18^F]BMS-986192 between patients and within tumor lesions of the same patient (primary tumor and TDLN/lymph node metastases) before treatment, in relation to changes in [^18^F]-FDG uptake before and on treatment

*Hypothesis: interpatient and intrapatient heterogeneity in tumor accumulation of [^18^F]BMS-986192 is expected and can be visualized. [^18^F]-FDG allows identification of viable tumor.*

2. To investigate the feasibility and safety of neoadjuvant nivolumab immunotherapy prior to surgery for locally advanced oral cancer.

*Hypothesis: neoadjuvant immunotherapy with nivolumab is feasible and safe, and will lead to immune activation and clinical response in a subset of patients.*

## Secondary objectives & hypotheses

3. To investigate effects of nivolumab treatment on PD-L1 expression and availability for tracer binding in the patient and the relation to (changes in) [^18^F]-FDG uptake.

*Hypothesis: changes in tumor accumulation of [^18^F]BMS-986192* *during treatment will occur and can be visualized.*

4. To investigate the relationship between [^18^F]BMS-986192 tumor uptake and tumor cell- and tumor infiltrating lymphocyte (TIL) PD-1 and PD-L1 expression as well as other immune parameters.

*Hypothesis: changes in tumor accumulation of [^18^F]BMS-986192* *during treatment will occur and can be visualized.*

5. To investigate changes in [^18^F]-FDG uptake during treatment.

*Hypothesis: Early changes on [^18^F]-FDG imaging on treatment will allow early response prediction.*

6. To investigate the genomic profile of the tumor (neoantigens, mutational load, copy number changes and splice variants), in relation to [^18^F]BMS-986192 uptake, immune activation parameters and clinical response.

*Hypothesis: immunotherapy with checkpoint inhibitors is most effective in tumors with high mutational load and head and neck cancers carry a large number of copy number changes, mutations and splice variants. We expect that when quantified, this relates to immune activation assuming presence of PD-L1 expression/uptake.*

7. To investigate blood based analyses of the immuneprofile and plasma vesicle miRNAs on treatment and after treatment, in relation to immune activation parameters and clinical outcome.

*Hypotheses: changes in the immune profile are a potential biomarker for immune activation in the tumor as detected in the surgical resection material. Changes in the plasma vesicle miRNA profile are a potential predictive and prognostic biomarker for clinical outcome.*

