### [18F]-FDG PET

As the treatment of HNSCC patients often involves multimodality treatment with surgery, radiotherapy and concomitant systemic therapy which causes extensive morbidity, early response evaluation could significantly improve quality of life and potentially survival as treatment can be adapted accordingly. A study with induction chemotherapy indeed showed promising results for predicting response in patients with significant reduction in the [18F]-FDG uptake in all lesions expressed as total lesion glycolysis (responders -85.9% ± 18.6 vs non-responders 36.4±64.1) [39]. In a meta-analysis the same conclusion was reached, early [^18^F]-FDG shows promise for response predication, however, standardized evaluation is required for further conclusions [40].

Regarding the usefulness of early [^18^F]-FDG imaging for patients treated with immunotherapy there is only limited evidence in literature so far. For patients with melanoma treated with a variety of immunotherapies including nivolumab [^18^F]-FDG changes showed mainly increase in [^18^F]-FDG uptake at 3 weeks after start of treatment in patients who responded at the later evaluation time points. These findings are consistent with immune activation in the tumor leading to increased glucose consumption [41].

Based on these results, early increase in [^18^F]-FDG uptake in patients with locally advanced oral cancer treated neoadjuvantly with nivolumab are expected to predict histopathological response in the resection material.

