## [^18^F]BMS-986192 and [^18^F]-FDG PET imaging acquisition

After inclusion and before panendoscopy, a [^18^F]BMS-986192 PET scan will be obtained for all patients. At VUmc, previous dynamic imaging with [^18^F]BMS-986192 has been performed to obtain data for kinetic modeling describing uptake, retention, and clearance of the tracer in tissue [58]. The steady state imaging timepoint for static whole body scanning has been set at 60-75 min after tracer injection. [^18^F]-FDG PET will be performed according to EANM guidelines [59]. To allow for ^18^F decay, [^18^F]-FDG PET and [^18^F]BMS-986192 PET will be performed with a minimum interval of 24 h time. PET-imaging will be done before panendoscopy (day 1 ±3, figure 1) and 21 days after nivolumab treatment (day 24±3, figure 1).

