## Treatment with nivolumab

On day 3 ±3, patients will be treated with a single flat dose of 480mg IV. Details on preparation, handling and dispensing info are provided in section 5.6. Product description information is provided separately [32, 57].

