## [^18^F]BMS-986192/[^18^F]-FDG PET procedure

All PET scans will be performed on a Philips Ingenuity TF PET/CT scanner. Each acquisition will start with a 30 mAs low-dose CT scan to correct for attenuation of the subsequent emission scan. A static total body PET scan after injection of 225 MBq ±10% [^18^F]BMS-986192 will be acquired at 60-75 min post injection. Static acquisition consists of 10-12 bed positions, depending on the length of the patient, of 3 minutes each.

[^18^F]-FDG PET will be performed in compliance with European Association of Nuclear Medicine (EANM) 2.0 guidelines [59], before and 21 ±3 days after start of treatment with nivolumab. Briefly, patients will fast 6 hours prior to the radiotracer injection. Patients will be injected with 3 MBq/kg (± 10%) [^18^F]-FDG. After 60 min (± 5 min) a PET scan will be performed from skull base to mid-thigh. The dose of [^18^F]-FDG will be about 185 MBq for PET (adapted by weight). Residual activity in the syringe will be measured and subtracted from the injected dose before calculations are done.

[^18^F]-FDG-PET and [^18^F]BMS-986192 PET will be performed with a minimum interval of 24 h to allow sufficient decay of the remaining tracer.

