## Tumor imaging and assessment of disease

Besides the [^18^F]BMS-986192 and [^18^F]-FDG PET scans, a baseline MRI of head and neck will be made for baseline tumor measurements. Early response evaluation with MRI will be performed just before surgery (day 24 ±3, [Figure 1](#Figure1)). As included in standard of care, a diagnostic CT of neck, thorax and abdomen will be performed before treatment.

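### The hypothesis under objective 5 promises early response prediction from FDG change, but every response in section 9.3 is read nominally 0 to 1 day from that FDG scan

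*Protocol*

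**What the plan says.** **The claim.** Objective 5 in section 2.2 is only to study how FDG uptake changes during treatment. The hypothesis beneath it goes further: early FDG changes on "imaging on treatment will allow early response prediction". Section 1.2.2 names the target, saying that early increases in FDG uptake "are expected to predict histopathological response in the resection material". The evidence it cites is a melanoma study that saw mainly an increase in FDG "uptake at 3 weeks after start of treatment in patients who responded at the later evaluation time points".

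**The schedule.**
- Section 3.3: "On day 3 ±3, patients will be treated with a single flat dose".
- Section 3.2 puts the second PET "21 days after nivolumab treatment (day 24±3, figure 1"), and section 5.3 puts FDG PET "before and 21 ±3 days after start of treatment with nivolumab".
- Section 7.12: "Early response evaluation with MRI will be performed just before surgery", with day 24 ±3 as its window. Section 3.5 agrees in substance.
- Section 7.19 lists Imaging II (both tracers and MRI) at day 24 ±3 and surgery at day 25 ±4.

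**The analysis.** Section 9.3 correlates SUV, percentage change in SUV and TLG with three classifications: RECIST 1.1, PERCIST and the Mandard grade. Section 5.5.2 takes the PERCIST category from the FDG data.

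**The concern.** Early prediction means that the marker is read clearly before the outcome. Here FDG change and the responses it is meant to predict are read almost together, so a correlation would be agreement between near-simultaneous readouts.

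Two misreadings could follow.
- A positive result could be carried into the larger randomised trial that section 1.1.2 has in mind as evidence that FDG is early enough to be useful. Section 1.2.2 motivates early evaluation by the chance to adapt treatment, but no such lead time is tested.
- A null result could be taken to refute the idea of an early FDG increase in responders. The cited melanoma study read response at later time points, whereas this trial reads it at about three weeks. A null result here would not bear on that lag.

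**Working it through.** **Inputs (study days)**
- Nivolumab: day 3 ±3, that is days 0 to 6 (sections 3.3 and 7.19).
- On-treatment FDG PET: day 24 ±3, days 21 to 27, and 21 ±3 days after nivolumab (sections 3.2, 5.3 and 7.19).
- Response MRI: day 24 ±3, days 21 to 27 (sections 7.12 and 7.19).
- Surgery: day 25 ±4, days 21 to 29 (section 7.19).

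**Reproducing the protocol's own figure.** Nivolumab day 3 + 21 = day 24, which matches section 3.2.

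**Lead time from FDG PET to each response in section 9.3**

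| Response | Source | Nominal gap | Range over the windows |
| --- | --- | --- | --- |
| RECIST | Imaging II MRI | 24 − 24 = 0 days | 21 − 27 = −6 to 27 − 21 = +6 days |
| PERCIST | the same FDG scans | none | none |
| Mandard grade | resection | 25 − 24 = 1 day | 0 to 29 − 21 = 8 days if PET is not after surgery |

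Taken independently, the windows would even allow surgery 27 − 21 = 6 days before the PET day. That is an artefact of combining windows, since the PET is meant to be preoperative.

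**How early is the scan in the treatment interval?** The fraction elapsed is (PET day − nivolumab day) / (surgery day − nivolumab day).
- Nominal: (24 − 3) / (25 − 3) = 21/22 = 95%.
- Lowest over all permitted combinations: nivolumab day 3, PET day 21, surgery day 29, giving 18/26 = 69%.
- Highest: 100%, when PET and surgery fall on the same day.

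So at least about two thirds, and nominally almost all, of the interval from dose to specimen has passed when FDG is read.

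**Side by side.** Section 3 calls FDG imaging an early readout of response, and section 9.3 plans a correlation. Both fit this schedule. The hypothesis under objective 5 and the last paragraph of section 1.2.2 claim more than it can support.

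**The case against.** The strongest reply is that this is wording only, and much of that stands. The words at issue are a hypothesis in a pilot that section 4.3 calls descriptive and hypothesis generating. The planned analysis is already a correlation. No treatment is adapted on the FDG result, so no participant is affected, and the remark in section 1.2.2 about adapting treatment is general background. The timing is largely set by the guideline interval to surgery (sections 1.2.6 and 3.6). Early can also mean early after starting treatment, and a scan read before the specimen is graded predicts pathology in the everyday preoperative sense. That sense is concurrent validity, however, and the phrase in the hypothesis promises more.

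A reader might infer several stronger points that the documents do not support.
- *That objective 5 itself claims prediction.* It does not; the hypothesis beneath it does.
- *That the trial can show nothing beyond concurrent agreement.* Patients are followed for 12 months after surgery (sections 3.7 and 7.15) and outcome data are collected (section 3). FDG change could be set against later outcome. Section 9.3 does not list this, but an analysis plan might.
- *That lead time is fixed at one day.* One day is nominal; the windows allow up to 8.
- *That objective 7 has the same fault.* Its hypothesis reads "Changes in the plasma vesicle miRNA profile are a potential predictive and prognostic biomarker for clinical outcome". Blood is taken at baseline, 10 and 21 days after nivolumab, and 1 and 3 months after surgery (section 7.11), so samples can precede later clinical outcome. Whether a single-arm trial can separate predictive from prognostic value is a different question. The text says only potential, and section 1.1.2 already says a randomised trial is needed to prove its clinical hypotheses.

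**Conclusion.** The point holds as a minor correction to what the trial may conclude. No response that section 9.3 relates to FDG change comes materially later than the FDG scan: 0 days nominally to MRI, none to PERCIST, and 1 day nominally to pathology (0 to 8 over the windows). Those analyses can support association or agreement at the time of surgery, not early prediction with useful lead time. An analysis plan cannot repair this for these responses, because the schedule in the protocol fixes it.

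This assumes that the scheduled windows are kept, that PET precedes surgery, and that response means the three classifications in section 9.3. It does not extend to later clinical outcome, and the sample size, primary endpoints and planned data are untouched.

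**What to change.** 1. Reword the hypothesis under objective 5 and the last paragraph of section 1.2.2 as *association of FDG change with MRI and pathological response at the time of surgery*.
2. State in section 9.3 that PERCIST is not an independent response measure for FDG change, because both come from the same scans.
3. If a forward-looking statement is wanted, add a purely descriptive analysis of FDG change against recurrence in the planned 12-month follow-up. State its limits: 15 evaluable patients, adjuvant treatment in between (section 7.14), and follow-up that can end when new anti-neoplastic therapy starts (section 7.15). As a rough guide, if the 40-50% recurrence or metastasis figure in section 1.1.2 applied here, it would mean 15 × 0.40 = 6 to 15 × 0.50 = 7.5 patients. That section gives no time horizon, so 12 months may see fewer.

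The cost is a slightly less favourable claim and, if item 3 is taken up, a little extra descriptive analysis. No new visits, scans or patients are needed.

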# STUDY DESIGN

In this pilot study we will study potential biomarkers and safety of nivolumab in a neoadjuvant setting combined with the routine treatment protocol applied for locally advanced oral cancer patients.

The routine diagnostic workup with MRI and [^18^F]-FDG imaging, and clinical examination using panendoscopy followed by surgical excision allows for 1) collection of tumor and TDLN/pathological lymph node specimens as well as blood samples before and after induction treatment with nivolumab and 2) pretreatment and on-treatment imaging with [^18^F]BMS-986192 and [^18^F]-FDG, respectively. Whole body tracer uptake analysis enables visualization of spatial and temporal heterogeneity of PD-L1 *in vivo* in the tumor and lymph nodes and the change of expression during treatment, and can be linked to routine immunostaining procedures. [^18^F]-FDG imaging allows the detection of viable tumor at baseline and an early readout for response during treatment. In order to investigate feasibility of the addition of nivolumab treatment to standard surgery, patients will be monitored closely for adverse events and outcome data will be collected.

